#### Secondary outcome measures

The length of hospital stay, cost, and quality of life, and the frequency of short term and long term complications will be compared between the short stitch and the long stitch group.

The length of hospital stay is defined as the time period from the day of surgery until the day of discharge.

The assessment of costs includes the material cost (suture), cost per operation minute (duration for abdominal wall closure), cost of hospital stay, and the cost saving per prevented incisional hernia.

To analyze quality of life, the EQ-5D-5 L questionnaire will be used and documented by the patient preoperatively, and after 30 days, 1 year, 3 years, and 5 years postoperatively. The EQ-5D-5 L is used in the German language version and a license has been obtained from the EuroQol Group by the sponsor. The EQ-5D is a standardized measure of health status developed by the EuroQol Group to provide a simple, generic measure of health for clinical and economic appraisal. The questionnaire is designed for self-completion by respondents and takes only a few minutes to complete. Instructions to respondents are included in the questionnaire. The EQ-5D-5 L consists of two pages a descriptive system and the EQ Visual Analogue Scale (EQ-VAS). The descriptive system comprises five dimensions (mobility, self-care, usual activities, pain or discomfort, anxiety or depression). Each dimension has five levels: no problem, slight problems, moderate problems, severe problems, and extreme problems. The EQ-VAS records the respondent’s self-rated health on a 20 cm vertical visual analogue scale with endpoints labeled ‘the best health you can imagine’ and ‘the worst health you can imagine’.

Short term complications include the frequency of burst abdomen and the reoperation rate due to burst abdomen until day of discharge. Wound infections occurring until the day of discharge and within 30 days after surgery will be recorded as short term complications. Wound infections are defined according to the US Centers for Disease Control and Prevention (CDC). Furthermore, wound healing complications, such as seroma, necrosis, and fistula, reported until 30 days postoperatively will be counted as short term complications.

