### Sample size calculation

The ISSAAC study has shown a risk of 19% of developing an incisional hernia within one year using MonoMax® suture material and a long stitch technique for abdominal wall closure of a primary elective midline laparotomy [14]. The aim of this study is to demonstrate that the short stitch suture technique with MonoMax® will decrease the incisional hernia rate after 1 year by 50% compared with the long stitch technique (primary endpoint). Considering hernia rates of 19% and 9.5% in both groups, a total sample size of 424 patients (212 per group) will be necessary to detect this difference with a power of 80% and an alpha of 5%. Including a drop-out rate of 10%, a total of 468 patients will be randomized in the current study. Thus, each of the seven participating centers should recruit about 67 patients. To avoid center effects, a maximum of 200 patients may be recruited per center. Withdrawn patients will not be replaced.

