### Statistical analysis

A planned analysis will be performed after all patients have completed their 1 year follow-up (primary endpoint). All data available until 1 year follow-up will be analyzed. Additional analyses will be conducted after completion of the 3 and 5 year follow-ups. It is intended to publish the 1 year result as well as the 3 and 5 year results in a peer-reviewed journal.

The statistical analysis of the primary endpoint has a confirmative character, whereas the secondary endpoints will be analyzed exploratively.

The description of the patient cohort with respect to demographic data and the baseline values of investigated parameters will take place as a whole as well as grouped by treatment group.

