### Secondary endpoints

Secondary endpoints will be tabulated as frequencies and rates, or as means and standard deviations, as appropriate. Confidence intervals will be used when appropriate.

The two-sided chi square test for independent proportions will be used for proportion comparisons. The Kaplan-Meier method will also be used to calculate other rates to be analyzed. For each such event, the date of occurrence must be recorded. The two-sided *t* test for independent samples will be used for comparisons with continuous variables.

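### EQ-5D-5L is recorded before randomisation, but the only stated comparison of continuous secondary outcomes is a t test without baseline or centre adjustment: lost precision, not bias

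*Protocol article*

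**What the plan says.** Protocol article, Secondary outcome measures: quality of life is one of the outcomes to be compared between the two suture groups. The EQ-5D-5L is "documented by the patient preoperatively, and after 30 days, 1 year, 3 years, and 5 years postoperatively". The section describes five dimensions, each with five levels, and a visual analogue scale (EQ-VAS). It does not mention an index score.

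Protocol article, Randomization: allocation takes place during the operation, shortly before the abdominal wall is closed, from a separate list for each centre. The preoperative questionnaire therefore precedes randomisation, and centre is a stratification factor.

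Protocol article, Statistical analysis, Secondary endpoints: the two-sided t "test for independent samples will be used for comparisons with continuous variables". No covariate, change score or repeated-measures model is named.

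Protocol article, Statistical analysis: the only stated use of baseline data is descriptive, in that the description of the cohort and "the baseline values of investigated parameters will take place as a whole as well as grouped by treatment group". The same section says that "the secondary endpoints will be analyzed exploratively".

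**The concern.** A score taken before randomisation usually predicts the same score at follow-up. Adjusting for it removes part of the patient-to-patient variation from the treatment comparison and costs nothing in data. The article collects this score and fixes a test for continuous variables, but gives the score no role in that test. The same holds for centre, although randomisation is stratified by it and the article caps recruitment per centre to avoid centre effects.

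At stake is the precision of the quality-of-life results, which are to be published at 1, 3 and 5 years. For an exploratory endpoint the estimate and its interval are the main product, so needless width matters somewhat even though no decision hangs on a p value.

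**Working it through.** **1. The plan's own figure.** The only sample size given is for hernia. Inputs from Sample size calculation are 19% and 9.5%, 80% power and 5% alpha, with the two-sided test taken from Primary endpoint. With the pooled two-proportion formula and mean rate 0.1425:

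n per group = [1.96 × √(2 × 0.1425 × 0.8575) + 0.842 × √(0.19 × 0.81 + 0.095 × 0.905)]² / 0.095² = (0.969 + 0.412)² / 0.009025 ≈ 211.4, so 212 per group and 424 in total.

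This matches the article. It does not involve quality of life, and nothing below changes it.

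**2. Inputs for quality of life.** The documents give no standard deviation and no baseline to follow-up correlation r. I assume r from 0.2 to 0.6. Low values are included because the preoperative score is set against visits as late as 5 years.

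**3. Formulas.** All are relative to the t test on follow-up scores:
- ANCOVA with the preoperative score: variance ratio 1 − r²; interval-width ratio √(1 − r²).
- t test on change from baseline, with equal variances at the two times: variance ratio 2(1 − r).

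| Assumed r | ANCOVA variance ratio | Variance cut | Width ratio | Interval narrower by about | Change-score variance ratio |
|---|---|---|---|---|---|
| 0.2 | 0.96 | 4% | 0.980 | 2% | 1.6 |
| 0.3 | 0.91 | 9% | 0.954 | 5% | 1.4 |
| 0.4 | 0.84 | 16% | 0.917 | 8% | 1.2 |
| 0.5 | 0.75 | 25% | 0.866 | 13% | 1.0 |
| 0.6 | 0.64 | 36% | 0.800 | 20% | 0.8 |

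**4. Simulation check.** With 212 per group and 4,000 runs, the simulated ANCOVA variance ratios were 0.92 at r = 0.3 and 0.74 at r = 0.5, against 0.91 and 0.75 from the formula.

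**5. Change scores.** The difference between the two ratios is 2(1 − r) − (1 − r²) = (1 − r)², which is never negative. Whichever way the sentence in Secondary endpoints is read, ANCOVA is at least as precise. For r below 0.5 the change-score test is worse than ignoring baseline altogether.

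**6. In units of the outcome.** With 212 per group, the difference detectable at 80% power by the t test is (1.96 + 0.842) × √(2/212) = 0.272 SD. Multiplying by the width ratio gives 0.267, 0.260, 0.249, 0.236 and 0.218 SD for the five values of r. This is only a translation of scale, since the article sets no power target for quality of life.

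The gain from adding centre is not quantified, because the documents give no between-centre variation in EQ-5D-5L.

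**The case against.** The case for leaving the plan alone has several parts.

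- **The t test is valid.** Under randomisation it is unbiased and controls the type I error. This stands. A reader might infer that chance imbalance in the preoperative score biases the result. It does not: the standard error of a baseline mean difference is √(2/212) = 0.097 SD, and that variation is already part of the t test's standard error. It is the precision loss described another way. Ignoring stratification by centre tends likewise to make the test conservative, not misleading.
- **The endpoint is exploratory, with no power claim.** This stands. The variance ratios could be turned into the extra patients a t test would need for equal precision (1/0.75 = 1.33 at r = 0.5), and a reader might conclude that the trial is too small for quality of life. The documents set no such requirement.
- **The wording is generic.** The sentence names neither the EQ-5D-5L nor the quantity compared, so it cannot be said outright that the baseline is discarded; change scores would fit the wording. This stands as a limit on the reading, but step 5 shows that it does not rescue the method.
- **The correlation is unknown and may be low at late visits.** This stands. At r = 0.2 the gain is slight.
- **Covariates belong in an analysis plan that is not shown.** This stands only in part. The article does not leave the method open; it names a test, and an analysis plan that follows it would run that test unadjusted.

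**Conclusion.** The point holds as a modest matter of efficiency. The article states an unadjusted comparison for continuous secondary outcomes although a pre-randomisation EQ-5D-5L score and a stratification factor are both available. The cost is an interval wider than necessary: adjustment would narrow it by about 2% to 20% for assumed correlations of 0.2 to 0.6. These figures rest on the assumed range, on a roughly linear relation between preoperative and follow-up scores, and on the t test being applied to follow-up scores. The direction is certain under either reading; the size is not.

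The documents do not support a claim of bias, type I error inflation or inadequate sample size. The hernia analysis and the 424 and 468 patients stand as they are. The text clearly applies to the EQ-VAS. It would apply to an index score only if one is derived, and a t test does not suit the five ordinal dimensions.

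**What to change.** In Secondary endpoints, replace the t test for the EQ-VAS, and for an EQ-5D-5L index if one is derived, by ANCOVA at each visit with treatment, preoperative score and centre. Report the adjusted difference with its 95% confidence interval.

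A mixed model for repeated measures is an acceptable alternative. Because separate analyses are planned after the 1-, 3- and 5-year follow-ups, each model should include only the visits available at that analysis; a single model over all visits cannot serve the 1-year report.

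The cost is a change of wording, made before the 1-year analysis. The preoperative score and the centre are already recorded, so no visit, questionnaire or patient is added. If the full protocol or the analysis plan already specifies such an adjustment, it is enough to bring the two texts into line.

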### Safety

Descriptive statistics methods will be used to analyze safety (listings and, when appropriate, frequency tables of relevant events by treatment group).

### Ethical and legal issues

The final study protocol was approved by the ethics committee of Vienna, Austria. Secondary approval was obtained from all local ethics committees responsible for the participating centers:Ethics committee of Vienna, Austria,Ethics committee ‘Landes Oberösterreich’, Linz, Austria,Ethics committee ‘Bundesland Salzburg’, Salzburg, Austria,Ethics committee of Ludwig Maximilian University, Munich, Germany,Ethics committee ‘Landesärztekammer Baden Württemberg’, Stuttgart, Germany,Ethics committee of University Tübingen, Germany.

Any substantial changes to the original documents will be submitted to the ethics committees in line with pertinent regulatory requirements.

This study will be carried out in accordance with the principles of the Declaration of Helsinki and in compliance with Good Clinical Practice. The trial staff will ensure the preservation of the pseudonymity of the patients. Upon inclusion in the study, each patient will receive a unique consecutive patient randomization number. The number consists of a five-digit code. The first two digits indicate the center and the following three digits stand for the sequential patient number.

### Quality control and assurance

Quality control will involve collecting data on adherence to the intervention, patient inclusion and follow-up, as well as monitoring the quality of data entry. Authorized qualified representatives of the sponsor will visit the participating clinics at regular intervals, as defined in the monitoring plan, to verify adherence to the protocol and local legal requirements, to perform source data verification, and to assist the investigator in study-related activities. Up to ten monitoring visits per center are planned, depending on the number of recruited patients.

Data will be entered in a database, as recorded in the paper-based case report form. To ensure data quality, double entry will be used. After completion of data entry, checks for plausibility, consistency, and completeness will be performed. Based on these checks, queries will be produced combined with queries generated by visual control. All missing data or inconsistencies will be reported to the centers and clarified by the responsible investigator.

## Discussion

For several generations of surgeons, the mass-layer single stitch suture has been the most common and standard technique for closure of the median incision. There is limited evidence that even with the ‘long stitch’ technique using a loop suture, only one layer, the fascia only, should be included [15] because there is less trauma to the tissue, implying a reduction in the risk of a burst abdomen. In addition to mesh development, today, different suture materials are available for closing the abdominal wall in primary laparotomies and incisional hernia surgery. Experimental studies and the clinical adaptation of an innovative ‘short stitch’ technique by the Israelsson study group [14,15] clearly proved, in a controlled trial, the concept of reduced tissue trauma and the impact on infection and incisional hernia rates when using this technique. Reducing the distance between the stitches and the wound edge to between 5 and 8 millimeters, thereby increasing the suture/wound length ratio, and using slowly absorbable sutures of size USP 2/0 (polydioxanone) and a half-circle round-bodied needle (thread length: 20 mm; arch length: 31 mm) and grasping only the aponeurosis, led to a significant decrease in the infection rate, as well as in the incisional hernia rate, compared with the ‘long stitch’ group. The average suture/wound length ratio of the ‘short stitch’ group of 5.7 versus 6.4 percent in the ‘long stitch group’ resulted in a significantly lower rate of wound infection of 5.2 versus 10.2 percent, as well as a highly significant lower incisional hernia rate of 5.6 versus 18 percent at the one-year follow-up. The multivariate analysis revealed a twofold risk of wound infection and a fourfold risk of incisional hernia occurring in the ‘long stitch’ group. Another randomized controlled trial, the STITCH study [16] obtained similar significant results when comparing the large versus short stitch technique of primary midline closure. The one-year results of this study were presented at the annual EHS-Meeting in Edinburgh in May 2014. The incisional hernia rate in the large stitch group was 23%, compared with 14% for the short stitch group. In comparison with the Millbourn study [14], the incisional hernia rate is more than twice as high in the short stitch group, using an identical suture material. The reason for this difference might be the complete follow-up of all patients by ultrasound. An increase in the incisional hernia rate by 60% from 12 months to 36 months postoperatively has to be taken into account, as detected in the recently published data by Fink *et al.* [17], regarding the long term follow-up of the INSECT and ISSAAC trials [18,13].

The significant advantage of the short stitch technique in causing minimal trauma to the abdominal wall seems to be clearly supported by the evidence-based level, whereas the synergetic effect of a special suture material used in this field has yet to be proven.

Based on the use of an elastic suture material with a long-lasting strength retention and ultra-long absorption time (MonoMax®), the ESTOIH study can be expected to yield lower hernia rates than the Millbourn study [13].

### Trial status

The study protocol was been registered on 9 October 2013. A first investigator meeting was held on 28 February 2014 in Munich, Germany. All centers have been initiated and are actively recruiting. The first patient was recruited on 6 March 2014. In total, 55 patients were randomized, while the manuscript was being completed. Recruitment is expected to end in December 2015.
